### Power Calculations and Estimation of Sample Size

Our sample size calculation was conducted based on examining the effect sizes of similar studies in the current literature [68]. Effect sizes for fruit and vegetable intake ranged from 0.41 to 0.8 [9,28]. Using the smaller effect sizes and considering the stepped wedge design as a clustered randomized trial, with an Interrelation Class Coefficient of 0.016 [37] estimated from the literature (thereby reducing our effective sample size), a total of 210 participants (105 per group) is required to reach 80% power. With an expected N*=*410 participants in the analytic sample (effective N=374), we will be able to detect an effect size of 0.30 with 80% power and 97.7% power to detect an effect of 0.41 [69]. To detect a difference with an effect size of 0.3 or greater with 80% power at an alpha level of 0.05, 352 participants are required in the analytic sample. Power was calculated using the stepped wedge command in STATA/SE (12.1; StataCorp LLC). The details are described in Hemming and Girling [36].

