**Methods:**

This proposed digital nutrition education intervention study targets technologically limited older adults enrolled in the congregate meal program (CMP) using a stepped-wedge clustered randomized controlled trial. Key community partners, City of San Antonio Department of Health Services Senior Services Division and OATS, contributed to the study’s planning phase, research design, and implementation. The 20-week intervention included 5 weeks of in-person technology training, including internet access and technical support for 1 year and devices, followed by 15 weeks of a culturally tailored online nutrition education intervention. The study randomized 398 older adults from 12 congregate meal sites. Data collection took place at baseline, 3 months, 6 months, 9 months, 12 months, and 18 months. If successful, the impact of this program could be applied throughout the national OATS network and to similar CMPs to bridge the digital divide beyond the COVID-19 pandemic.

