#### Statistical Models

##### Aim 1

Primary outcome data will be analyzed in Aim 1. For each of the 3 outcomes in Aim 1 (Dietary Quality Score and Food Security), at 3-month and 6-month periods, a 2-level multilevel model (MLM) will be constructed that examines change over time for individual participants within centers. MLMs consider that participants within a cluster (eg, a center) share characteristics that make them more like each other than participants at other centers. MLM has several distinct advantages over other modeling strategies: (1) MLM has greater statistical power given that the estimated standard errors are corrected for model dependency; (2) there is no need to assume or test for the homoscedasticity or sphericity assumptions, as these variance and covariance components are estimated within the MLM model. Depending on model complexity and whether the statistical assumptions are met, the models will be estimated via Bayesian estimation or maximum likelihood estimation with robust standard errors. For Level 1 (participant level), the outcome variable of interest will be modeled using pretest score on the outcome measure, treatment status (ie, control or experimental), and any nonequivalent baseline participant characteristics as covariates. Level 2 (center level) will model the cluster effect of centers on outcomes.

##### Aim 2

Data collected for Aim 2 represent our secondary research questions (eg, physical activity, technology knowledge and attitudes, social isolation, and loneliness). Data collected at all time points (Physical Activity Scale for the Elderly [PASE], technology knowledge and attitudes, social isolation, and loneliness) will be analyzed using MLM described in Aim 1. To minimize participant fatigue, data for this secondary research aim will be collected at defined intervals (T0, T1, and T2). These data will include the Healthy Eating Index and Short Physical Performance Battery (SPPB) to assess physical function. Differences between groups will be assessed at T2 for each outcome via 2-level covariate MLM models. Level 1 (participant level) will test whether treatment status (ie, control or experimental), pretest score on dietary quality, and food security, and any nonequivalent baseline participant characteristics predict outcomes. At Level 2 (center level), we will model the influence of the 7 centers.

##### Aim 3

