## Results

The project was funded in October 2022. As indicated in the study progress (Figure 3), recruitment and screening started in June 2022. The research team recruited and screened 150 participants by the end of August 2022 at the 7 original target centers. Due to the low recruitment numbers, the number of centers and recruitment time were extended. Seven additional centers for recruitment were incorporated starting in September 2022. Power analysis was completed to ensure adequate recruitment numbers were met with the 14 centers. NIH was notified in writing of these changes. Fourteen centers were condensed to 12 centers (1 closed because of structural damage and 1 smaller center merged with a larger sister center).

A total of 578 older adults completed the screening, of whom 507 participants were eligible to participate in the study (88%). The 12 centers were randomly assigned into 2 study cohorts, which consisted of a total of 398 older adult participants. Cohort 1 consisted of 226 eligible participants, of whom 164 participants graduated from the program. Cohort 2 had 172 eligible participants, of whom 111 participants graduated from the program (Figure 4). Monthly bingo and informative presentations (nonnutrition and nonphysical activity–related) were conducted with Cohort 2 centers for engagement and retention. Focus groups were conducted for Cohort 1 postintervention in October 2023 and for Cohort 2 in June 2024 to assess the fidelity of the intervention. Data collection for Cohort 2 is currently ongoing. Preliminary data analysis is being conducted for all cohorts to evaluate the intervention’s outcomes.

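### The effective sample size of 374 implies about 7 participants per center, so the stated power does not follow from the ICC and the 12 randomized centers

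*Protocol article*

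**What the plan says.** The section Power Calculations and Estimation of Sample Size describes its approach as "considering the stepped wedge design as a clustered randomized trial". Clustering enters through a single parameter, which the section introduces this way: "with an Interrelation Class Coefficient of 0.016 [37] estimated from the literature (thereby reducing our effective sample size". The figures it then reports are:

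- 210 participants (105 per group) for 80% power at an effect size of 0.41.
- An expected analytic N of 410, about which it writes: "participants in the analytic sample (effective N=374), we will be able to detect an effect size of 0.30 with 80% power". For an effect of 0.41 the power claimed at this N is 97.7%.
- A requirement for 0.30 at 80% power and alpha 0.05, worded as "352 participants are required in the analytic sample".

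On software, the section says: "Power was calculated using the stepped wedge command in STATA/SE".

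The paragraph gives no number of centers, no participants per center and no correlation other than the ICC.

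The center counts are elsewhere. The Results section describes 7 original target centers, 7 added later, and 14 condensed to 12. The abstract reports: "The study randomized 398 older adults from 12 congregate meal sites". The Aim 2 model in Statistical Models still says "we will model the influence of the 7 centers".

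**The concern.** In a cluster trial the loss of information depends on the ICC and on how many people share a center. The drop from 410 to 374 is small for 410 people spread over a dozen centers. If the cluster size behind it is wrong, then the effective N and the powers read from it are wrong as well.

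This paragraph is the only justification of sample size in the article. A reader will take it that the trial had 80% power for 0.30, and may read a null result as evidence against an effect of that size. The 352 invites a second misreading: 398 randomized exceeds 352, so the requirement looks met with room to spare, although 352 makes no allowance for clustering.

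**Working it through.** **Inputs.** From the power section: ICC 0.016, N = 410, effective N = 374, effect sizes 0.30 and 0.41, 80% power, alpha 0.05. Sidedness is not stated; two-sided is assumed and it reproduces the figures. From the Results section: 12 centers and 398 participants randomized, after 7 original and then 14 centers.

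**Formulas.** Design effect DE = 1 + (m − 1) × ICC, with m participants per center. Effective N = N / DE. Power ≈ Φ(d × √(effective N) / 2 − 1.96), for two equal groups and SD 1.

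**Step 1: reproduce the stated figures.**

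- 410 / 374 = 1.0963, so m = 1 + 0.0963 / 0.016 = 7.02. Only m between 6.92 and 7.11 gives an effective N that rounds to 374 (m = 6 gives 379.6, m = 8 gives 368.7).
- With m = 7, DE = 1.096 and 410 / 1.096 = 374.1.
- At 374, power for 0.41 is Φ(3.964 − 1.96) = 97.7%, as stated. Power for 0.30 is 82.7% (82.5% by t-test), slightly above the stated 80%.
- For 0.41, an unclustered t-test needs 95 per group. 95 × 1.096 = 104.1, rounded up to 105, which gives the stated 210.
- For 0.30, an unclustered t-test needs 176 per group, or 352 in total. No design effect has been applied. Even 1.096 would make it 352 × 1.096 = 386.

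So 374, 97.7%, 210 and 352 all follow from a two-sample t-test with a design effect of 1.096 or none.

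**Step 2: put in the center sizes that the article supports.**

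| N / centers | m | DE | Effective N | Power at 0.30 | Power at 0.41 |
|---|---|---|---|---|---|
| 410 / 12 | 34.2 | 1.531 | 268 | 69% | 92% |
| 398 / 12 | 33.2 | 1.515 | 263 | 68% | 91% |
| 410 / 14 | 29.3 | 1.453 | 282 | 71% | 93% |
| 410 / 7 | 58.6 | 1.921 | 213 | 59% | 85% |

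For 410 in 12 centers, the effect detectable with 80% power is (1.960 + 0.842) × √(4 / 267.9) = 0.34. With a t reference on 12 − 2 = 10 degrees of freedom instead of the normal, the powers in that row fall to about 60% and 86%.

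**Step 3: required numbers with 12 centers.** Setting N / (1 + (N/12 − 1) × 0.016) = E gives N = 0.984 E / (1 − 0.016 E / 12).

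- E = 352: N = 346.4 / 0.5307 = 653, against the stated 352.
- E = 190: N = 187.0 / 0.7467 = 250, against the stated 210.

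**Step 4: what the repeated measures could add.** Steps 2 and 3 describe a comparison after intervention only. A closed-cohort calculation for 410 people in 12 centers, 6 per cohort, was run with data at baseline and 6 months, or at baseline, 6 and 12 months. Assuming within-person correlation from 0 to 0.7 and cluster autocorrelation from 0.8 to 1, with a normal reference, power for 0.30 ranges from about 73% to over 99%. None of these correlations is in the article.

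**The case against.** The strongest reply is that about 69% is not the power of the planned analysis. The Aim 1 model includes the pretest score, and the design is a closed cohort measured repeatedly. Step 4 shows that this can bring power for 0.30 to 80% or above. That stands, and it limits the conclusion. It does not rescue the printed figures: the paragraph states no such correlations, claims no such credit, and its numbers follow from a simple design effect. A reader might infer that the trial is underpowered; the article does not support that.

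The Results section also says that a power analysis was completed for the 14 centers. Its inputs are not shown, so it is unclear which calculation the power section reports. Fourteen centers do not give 374 either: 29.3 per center gives 282, and m = 14 gives 339.

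It is tempting to state as fact that the number of original centers was entered as the cluster size. The article never writes this. It is a back-calculation, made plausible by the 7 original centers and the leftover 7 in the Aim 2 model. What is shown is only that 374 fits no average center size in the document.

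A reader might also add up the graduates, 164 in Cohort 1 and, in Cohort 2, "Cohort 2 had 172 eligible participants, of whom 111 participants graduated from the program", and set the sum of 275 against the required 352. That comparison fails. Graduating means completing the program, not supplying outcomes. Data collection events are separate and separately compensated, and full information maximum likelihood keeps non-graduates who have data. Cohort 2 also contributes control data before its own intervention. The article does not give the number with 6-month outcomes.

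Finally, the gap between 82.5% and the stated 80% at 374 is mild conservative rounding and not the error.

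**Conclusion.** The point holds as one about the stated figures. An effective N of 374 from 410 participants is not consistent with an ICC of 0.016 and any center count in the article. By the paragraph's own method, 12 centers give an effective N of about 268 (263 for the 398 randomized). Power is then about 69% rather than 80% for 0.30, and about 92% rather than 97.7% for 0.41, with a detectable effect of about 0.34. The 352 is an unclustered number presented as an analytic-sample requirement; the matching figure in 12 centers is about 653. The 210 becomes about 250.

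These values assume two-sided alpha 0.05, equal groups, equal center sizes, a normal reference and a post-only parallel comparison. The stated power is therefore unsupported. Whether the trial reaches 80% for 0.30 depends on correlations that the article does not give.

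**What to change.** Restate the power paragraph for the trial as randomized: 12 centers with their actual sizes, ICC 0.016 and the expected analytic N. Two routes are open:

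- As a cluster trial: a design effect of about 1.51 and an effective N of about 263 at 398 participants, before attrition, with the resulting power for 0.30 and 0.41 and the detectable effect.
- As a true stepped-wedge or baseline-adjusted calculation, with the assumed within-person and between-period correlations stated and a range shown.

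In either case, label 352 as an effective (unclustered) number, correct or drop the 210, and name the stepped-wedge command only for figures that come from it.

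The cost is rewriting one paragraph and possibly rerunning one calculation. On the first route the stated power becomes less favourable. No extra enrolment is proposed, and the analysis model is not affected.

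### The effective sample size of 374 implies about 7 participants per center, a size no center count in the protocol supports; by the same route, 410 in 12 centers gives about 268 and 69% power at 0.30

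*Protocol article*

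**What the plan says.** The section Power Calculations and Estimation of Sample Size treats the stepped wedge as a clustered randomized trial. For an effect size of 0.41 it works "with an Interrelation Class Coefficient of 0.016 [37] estimated from the literature (thereby reducing our effective sample size), a total of 210 participants", that is 105 per group, for 80% power. It then takes "410 participants in the analytic sample (effective N=374") and claims "effective N=374), we will be able to detect an effect size of 0.30 with 80% power and 97.7% power" at 0.41. It gives neither a cluster size nor a number of clusters, and it says that a stepped wedge command in Stata was used.

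The center counts stand elsewhere. The Results section reports early recruitment "at the 7 original target centers", the addition of seven more, a power analysis for 14 centers, and a reduction to 12. The Abstract states: "The study randomized 398 older adults from 12 congregate meal sites". The Aim 2 model under Statistical Models still says "we will model the influence of the 7 centers".

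**The concern.** A clustering allowance depends on how many people share a center. The printed allowance is under 10%, which looks small for a trial with some 400 people in a dozen centers. If the cluster size behind it is wrong, every figure built on it is too favourable: the effective N, the power at 0.30 and 0.41, and the 210. Readers use these figures to judge which effects the trial was designed to detect, and so would take 0.30 as covered at 80% power when the method used does not show that.

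**Working it through.** **Inputs.** From the power section: N = 410, effective N = 374, ICC = 0.016, effect sizes 0.30 and 0.41, alpha 0.05, equal groups. From the Abstract and Results: 398 randomized in 12 centers; 7 original centers; 14 after extension. Two-sided testing is assumed because it reproduces the printed figures.

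**Formulas.** Design effect DE = 1 + (m − 1) × ICC, with m the mean number of participants per center. Effective N = N / DE. Two-group power (normal) = Φ(d × √(effective N) / 2 − 1.96). Detectable effect at 80% power = (1.96 + 0.84) × 2 / √(effective N).

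**Step 1: reproduce the printed figures.**
- Implied DE = 410/374 = 1.0963, so m = 0.0963/0.016 + 1 = 7.02.
- Rounding of 374 (373.5 to 374.5) allows m from 6.92 to 7.11. Checking integers: m = 6 gives 410/1.080 = 379.6; m = 7 gives 410/1.096 = 374.1; m = 8 gives 410/1.112 = 368.7. Only 7 fits.
- Power on 374 people at 0.41: 0.41 × 19.34/2 − 1.96 = 2.00, so 97.7%, as printed.
- Power on 374 people at 0.30: 82.7% (normal) or 82.5% (t). This agrees with the printed 80% only if that means at least 80%.
- Without clustering, 0.41 needs 94.4, so 95 per group (t). Then 95 × 1.096 = 104.1, rounded up to 105 per group, or 210.

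The 374, the 97.7% and the 210 therefore all follow from a factor of 1.096 and a plain two-group test.

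**Step 2: compare 7 with the center sizes.** 410/12 = 34.2; 410/14 = 29.3; 410/7 = 58.6; 398/12 = 33.2. None is near 7.

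**Step 3: same method, mean center size put in.**

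| Participants / centers | m | DE | Effective N | Power at 0.30 | Power at 0.41 | Detectable effect |
|---|---|---|---|---|---|---|
| As printed (410) | 7 (implied) | 1.096 | 374 | 80% | 97.7% | 0.30 |
| 410 / 12 | 34.2 | 1.53 | 268 | 69% | 92% | 0.34 |
| 398 / 12 | 33.2 | 1.515 | 263 | 68% | 91% | 0.35 |
| 410 / 14 | 29.3 | 1.45 | 282 | 71% | 93% | 0.33 |
| 410 / 7 | 58.6 | 1.92 | 213 | 59% | 85% | 0.38 |

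For 410 in 12 centers: DE = 1 + 33.17 × 0.016 = 1.531; 410/1.531 = 267.9; 0.30 × 16.37/2 − 1.96 = 0.495, so 69%.

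**Step 4: the 210.** In 12 centers m = 17.5, DE = 1 + 16.5 × 0.016 = 1.264, effective N = 166, and power at 0.41 is about 75%, not 80%.

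**Step 5: sensitivity to the reference distribution.** A t reference with 10 degrees of freedom (12 centers less 2) lowers the 69% to about 60% and the 92% to about 86%. The protocol names no degrees of freedom, so this shows direction only.

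The 352 in the same section equals 2 × 176 with no clustering allowance and is a separate matter.

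**The case against.** The strongest objection is that the planned analysis is not the unadjusted two-group comparison recomputed above. The Aim 1 model includes the pretest score, the design is a closed cohort with repeated measurement, and the power section names a stepped wedge command. This has force. The documents give no correlations, so the following rest on assumed values, with 410 people in 12 centers, ICC 0.016 and an effect of 0.30:
- Pretest adjustment, if it removes center-level and person-level variance in equal proportion, makes the effective N 268/(1 − r²). Power is about 73%, 81% and 93% at r = 0.3, 0.5 and 0.7.
- Baseline plus 6 months with a constant center effect and within-person correlation 0 to 0.7: about 75% to 99%.

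A reader might therefore infer from the table that the trial is underpowered under its planned model. The documents do not support that: such a model may recover part or all of the stated power. But the objection does not rescue the printed figures, which use no such correlation and follow from a simple design effect at m = 7.

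A reader might also take it as established that the number of centers was entered in place of the center size, or that the section is left over from the 7-center plan. Both are plausible, since 7 was the original number of centers. Neither is documented: no formula is shown, and the Results section does not say whether the printed figures come from before or after the power analysis for 14 centers. The error does not depend on its cause.

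Finally, enrollment is complete, and no estimate, test or confidence interval changes. That limits the consequence to the reported sample-size justification.

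**Conclusion.** The point holds for the calculation as printed. At an ICC of 0.016, 374 requires 7 people per center, and none of the center counts in the article (7, 12 or 14) gives fewer than about 29. By the section's own method, 410 in 12 centers gives an effective N of about 268 instead of 374, power of about 69% instead of 80% at 0.30 and about 92% instead of 97.7% at 0.41, and a detectable effect of about 0.34. For the 398 randomized, these are about 263, 68%, 91% and 0.35. The 210 gives about 75% power at 0.41.

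These figures assume equal center sizes, the stated ICC, a two-sided 5% test with a normal reference, and no loss to follow-up. They do not measure the power of the pretest-adjusted or stepped-wedge model.

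**What to change.** In Power Calculations and Estimation of Sample Size, state the number of centers and the center sizes, recompute the design effect from them, and restate the effective N, the power at 0.30 and 0.41, the detectable effect and the 210. The replacement for 210 depends on whether the number of centers or the center size is held fixed, so the section should say which.

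Alternatively, report the pretest-adjusted or stepped-wedge calculation that matches the planned model, and state and justify the pretest and within-person correlations it assumes. Either way, the number of centers should agree with the Aim 2 model text, which still refers to 7.

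This is a text change and needs no extra participants. The cost is a less favourable stated power unless those correlations can be justified.

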### Data Analysis

#### Baseline Equivalency

Baseline characteristics for each cohort at the individual and cluster level will be used to determine if any imbalances exist in either demographic variable or baseline dietary intake and food security. Effect sizes (ES) for differences between cohorts will be assessed with Hedges *g* (for continuous variables) and Cox index (for dichotomous variables). Any variables with effect size between .05 and .25 will be added to models to adjust for pre-existing differences.

#### Missing Data

Missing data will be imputed using full information maximum likelihood. As with most longitudinal studies, participants leave the study at different times, with attrition commonly increasing over time. Traditional methods of handling missing data require the researcher to discard data or impute unknown values, which frequently causes estimation bias and loss of statistical power. These missing data concerns are ameliorated when using full information maximum likelihood, as it does not have the same limitations as other more common approaches (eg, listwise deletion and regression imputation methods).

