Successful dietary behavioral change interventions with older adults have common features including using behavior change theories to promote self-efficacy, containing clear and repeated messages, incorporating incentives for motivation, and sufficient contact [22,23]. Positive behavior change has successfully increased fruit and vegetable intake and fiber in interventions targeting community-dwelling older adults [24]. Interventions at congregate meal sites have successfully increased participant fruit and vegetable intake after a 5-session program [25] or a 4-week intervention [26]. Additional studies have documented improvements in nutrition risk scores, a small improvement in food-related behaviors for both congregate and homebound meal participants [27], and improvements in dietary supplement knowledge and behaviors in congregate meal participants [28].

Limited studies on digital interventions for older adults impacting nutrition exist, and published studies focus on eHealth or Telehealth [29,30] and disease-specific interventions [31-35]. Successful digital interventions have been documented using “telemonitoring” for 4 months to improve nutritional status and increase vegetable, fruit, and dietary fiber intake in a Dutch population [30]. This study observed a high level of participant satisfaction, with an 80% completion rate. The majority of dropouts were older and had poorer cognition and physical function [29]. Another telemedicine intervention had positive outcomes of reduced malnutrition and improved protein intake [33]. In interventions targeting specific disease states, evidence supports “eHealth” interventions using the web and mobile-based technologies to improve diabetes care [34], and an 8-week program to increase calcium intake and exercise to improve bone health [35].

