Frequency of Forgetting questionnaire		Measured at baseline, 6 months, and 6-month postintervention.	Assesses subjective memory impairments in older adult participants [65]. Scoring is based on the following categories: major problems, some minor problems, and no problems.
Activities of daily living questionnaire		Measured at baseline, 6 months, and 6-month postintervention.	The PhenX Toolkit was used to assess activities of daily living at baseline, 6 months, and 12 months [66]. Participants completed a 16-question survey and ability to complete activities: bathing, grooming, dressing upper body, dressing lower body, feeding, using toilet, walking, and getting in/out of chair.
Height, weight, and BMI		Measured at baseline, 6 months, and 6-month postintervention.	Measured without shoes and with lightweight clothing using a calibrated scale (Seca 876) and portable stadiometer (Seca 213). BMI will be calculated from the measured height and weight and will be used as part of the MNA score calculation. BMI categories are classified as follows: BMI less than 19=0, BMI 19‐20.9=1, BMI 21‐22.9=2, and BMI 23 or above =3 [67].
Demographic information and medical history		Gathered during screening.	Gathered responses on age, sex, residence zip code, senior center attended, race/ethnicity, who lives in the household, how many people live in the household, annual household income, education (highest level attended), current employment status, history of smoking, whether receiving benefits such as social security, disability, Supplemental Food Assistance Program (SNAP) or retirement benefits, diagnosis of medical conditions, and medication list.

a OATS: Older Adults Technology Services.

b UCLA: University of California, Los Angeles

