To assess the long-term impacts of the program at T3, Level 1 (time) will model the change in the outcome variables throughout the study (T0, T1, T2, and T3) within each participant. Specifically, each participant’s random intercept (eg, initial status) and the random slope over the 3 time periods will be calculated, and the time variable will represent the change in a particular outcome variable (ie, food security) over time within each participant. Level 2 (time nested within participant characteristics) will test whether treatment status (ie, control or experimental) and any nonequivalent baseline participant characteristics predict outcomes. If the ICC coefficient is greater than 0.10, a third level will be added to the model to control for clustering by center. Finally, participants will be clustered within centers (Level 3).

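### The likelihood method relied on for dropout is not tied to the variables expected to predict dropout, because baseline covariates enter the models only through cohort imbalance

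*Protocol article*

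**What the plan says.** All references are to the protocol article.

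- **Missing Data.** The method is stated in one line: "Missing data will be imputed using full information maximum likelihood". The section anticipates attrition that rises with time, contrasts the method with listwise deletion and regression imputation, and concludes: "These missing data concerns are ameliorated when using full information maximum likelihood". It states neither the missing-at-random condition nor any auxiliary variables.
- **Statistical Models, Aim 1.** The participant level contains "pretest score on the outcome measure, treatment status (ie, control or experimental), and any nonequivalent baseline participant characteristics as covariates"; the second level is the center. Aim 2 uses the same kind of model. Aim 3 models the repeated outcomes T0 to T3 with a random intercept and slope, plus treatment status and nonequivalent baseline characteristics.
- **Baseline Equivalency.** A variable enters if its between-cohort effect size lies between .05 and .25. Demographic variables, baseline dietary intake and food security are named for this screen.
- **Introduction.** On a cited digital nutrition program: "The majority of dropouts were older and had poorer cognition and physical function".
- **Table 2.** Age is gathered at screening. The Frequency of Forgetting questionnaire, measured at baseline, is described thus: "Assesses subjective memory impairments in older adult participants". An activities of daily living questionnaire is also given at baseline. The Short Physical Performance Battery (SPPB) is timed relative to each cohort's own intervention.
- **Results.** Of 226 participants in Cohort 1, 164 graduated. For the other cohort: "Cohort 2 had 172 eligible participants, of whom 111 participants graduated from the program".

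**The concern.** Full information maximum likelihood gives valid estimates when data are missing at random given the variables in the likelihood. If a variable drives both dropout and the outcome and is left out, that condition fails and the method does not repair the loss. The article selects covariates by a different criterion, cohort imbalance. A variable can be perfectly balanced and still be the main reason people leave.

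The matter is sharpest for the primary outcomes. The Aim 1 models, as described, have a participant level and a center level with pretest as a covariate, so each takes one follow-up value per person. When only that value is missing, a person without it contributes almost nothing to the treatment estimate, and the likelihood analysis is close to a complete-case analysis. The advantage over listwise deletion claimed in Missing Data is then largely absent unless further predictors are included.

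The two conditions also differ in what they ask of participants: tablet use, Zoom, Google Classroom and weekly surveys on one side, monthly talks and bingo on the other. It is plausible, though not shown, that memory or functional problems affect dropout differently under the two. That is the situation in which omission matters.

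**Working it through.** **1. Yardstick.** The power section sizes the trial for an effect of 0.30 with 352 participants. For a two-sided 5% test and 80% power, the normal approximation per group is 2 × (1.960 + 0.842)² / 0.30² = 174.4, so 175; with the t distribution it is 176, and 2 × 176 = 352. The figure reproduces. Biases below are expressed against 0.30. Missing Data gives no figure of its own.

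**2. Proxy for dropout.**
- Cohort 1: (226 − 164)/226 = 62/226 = 27.4%
- Cohort 2: (172 − 111)/172 = 61/172 = 35.5%
- Overall: 123/398 = 30.9%

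These are non-graduates, not missing outcome values.

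**3. Does the entry rule bring the predictors in?** Take a screened variable with no true cohort difference. The standard error of Hedges *g* is about √(1/226 + 1/172) = 0.101, and

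P(0.05 < |g| < 0.25) = 2 × [Φ(0.25/0.101) − Φ(0.05/0.101)] = 0.61.

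Allowing for clustering with the article's ICC of 0.016 and 398/12 = 33.2 people per center, the design effect is 1 + 32.2 × 0.016 = 1.515, the standard error 0.125 and the probability 0.64. If age, cognition and function were all screened and independent, all three would enter with probability of about 0.22 to 0.27. A |g| above 0.25 (probability 0.01 to 0.05) lies outside the stated band. Entry is therefore largely a matter of chance.

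**4. Size of the bias if a predictor is left out.** Let X be a dropout predictor (higher is worse), with the outcome coded so that higher is better. To first order,

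bias ≈ b × (mean of X given pretest among observed Cohort 1 − the same among observed Cohort 2),

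where b is the effect of X on the outcome beyond pretest. If dropout selects alike in both cohorts, the bracket nearly cancels.

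A large-sample simulation (one million per cohort, no clustering) puts numbers on this. From the article, as proxy: 27.4% and 35.5% missing. Assumed: true effect 0.30 SD, pretest slope 0.5, correlation of X with pretest −0.2, b from −0.1 to −0.3 SD, and the log-odds of dropout per SD of X shown below. The estimate is adjusted for pretest but not for X. Bias in SD units, positive favoring the program:

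| Log-odds per SD of X, Cohort 1 / Cohort 2 | b = −0.1 | b = −0.2 | b = −0.3 |
|---|---|---|---|
| 0.7 / 0.7 | −0.004 | −0.009 | −0.017 |
| 0.7 / 0.35 | +0.006 | +0.008 | +0.016 |
| 0.7 / 0 | +0.019 | +0.033 | +0.051 |
| 1.0 / 0 | +0.023 | +0.044 | +0.066 |
| 0 / 0.7 | −0.021 | −0.043 | −0.067 |

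As a check on the formula, the third row at b = −0.3 implies a difference of 0.051/0.3 = 0.17 SD in X between the observed groups.

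With differing mechanisms the absolute bias runs from 0.006 to 0.067 SD, that is 0.006/0.30 = 2% to 0.067/0.30 = 22% of the planned effect. With X in the model it stays within 0.003 SD of zero in every scenario.

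**The case against.** The strongest reply is that the article says little that is false. It claims only that the concerns are lessened, names a recognized method, and nowhere rules out auxiliary variables. A list of such variables is commonly left to an analysis plan, which is not shown. This stands in part: the absence of a list is no finding. What remains is that the article itself fixes the model terms and an imbalance-only entry rule, and these do not carry the protection it describes.

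Four stronger readings are tempting, and the document does not support them.

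- *That the models leave out age, cognition and function.* Age is a demographic variable and is screened, and Aims 1 and 3 admit any nonequivalent baseline characteristic. The accurate statement is that entry is not ensured, most clearly for cognition and function. In Aim 3 the repeated outcomes also carry some information about dropout.
- *That these variables drive dropout in this trial.* They come from one cited program in a Dutch population. This trial excludes diagnosed dementia and adds in-person training, technical support and peer navigators.
- *That 27% to 35% of outcomes are missing.* Data collection is separate from graduation and has its own gift card. Cohort 2's figure arises from an intervention begun after Cohort 1 had finished, so it says nothing direct about control-period losses at 3 and 6 months.
- *That the result will be biased in favor of the program.* This follows only if selective dropout is confined to, or stronger in, the treated cohort. A common mechanism gives a small bias the other way, and the reverse pattern gives one as large against the program.

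**Conclusion.** The point holds in a limited form. The article relies on full information maximum likelihood for attrition, yet its covariate rule does not ensure that the predictors cited in its own Introduction are in the likelihood. For Aim 1, read as one follow-up adjusted for pretest, the method then offers little beyond complete cases if such variables drive dropout.

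The likely size is modest: no more than 0.017 SD with a common dropout mechanism, and about 0.01 to 0.07 SD in either direction with differing ones. These figures rest on assumed slopes, correlations and dropout odds, and on non-graduation standing in for missing outcomes. They show what could happen and do not estimate what did. Since the remedy uses baseline values already collected, this is a free improvement and not a flaw that undermines the trial.

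**What to change.** In Missing Data, state that the method assumes data are missing at random given the variables in the model. In Missing Data and Statistical Models, prespecify baseline age, Frequency of Forgetting and activities of daily living as auxiliary variables or covariates for the Aim 1 to 3 outcomes, whatever their balance between cohorts. The imbalance screen can stay for other variables.

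Add SPPB only if a T0 value exists for both cohorts. Table 2 places its first measurement before the assigned intervention, which for Cohort 2 could fall after the control period; Aim 2 lists T0; and the Design section's account of Time 0 data does not name it. If no common T0 value exists, activities of daily living can represent physical function.

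The cost is a sentence or two and a few lines of model code, with no new data collection. Reporting missingness by cohort at 3 and 6 months would show how much the change matters.
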